The primary outcome measure will be the YGTSS-TTS (22), administered by a clinician blinded to the randomization condition. The raters will be psychiatrists or psychiatry residents, clinical psychologists, psychologists under training or psychology students receiving supervision. The raters will receive training in administering the YGTSS and participate in at least two test ratings with subsequent supervision before they are allowed to conduct assessments in the trial. Co-ratings will be arranged every 6 months for the active raters during the data collection period. Data on inter-rater reliability will be reported.

Secondary clinician-rated outcome measures will be the YGTSS-Impairment, as well as the Clinical Global Impression—Severity and Improvement (CGI-S and CGI-I, the latter not administered at pre-treatment) (23). The clinicians will receive training in administering the CGI that will be repeated every 6 months. Participants that are rated as “much improved” or “very much improved” on the CGI-I will be classified as treatment responders (24). If the participant keeps the responder status at subsequent follow-ups, they will be classified as long-term responders at that follow-up.

Self-rated tic-specific outcome measures will be the Adult Tic Questionnaire (ATQ) (also administered weekly) (25), the Gilles de la Tourette Syndrome—Quality of Life Scale (GTS-QoL) (26), and the Work and Social Adjustment Scale (WSAS) (27) adapted for TS/CTD by the research team. General quality of life will be measured using the Assessment of Quality of Life—6 Dimensions (AQoL-6D) (28), and these scores will be used in the health-utility analysis (see below). Symptoms of depression will be assessed using Montgomery-Asberg Depression Rating Scale—Self-report (MADRS-S) (29) (also administered at week 3 and 7). The self-reported Treatment Inventory of Costs in Patients with psychiatric disorders (TIC-P) will be administered to measure health-related costs (30).

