### Statistical methods

2.7

The significance level for all statistical tests will be *α* = 0.05. For all scale level measures, Cohen's d will be used as a measure of effect size. Odds ratios will be reported for categorical variables. Confidence intervals (95%) will be reported for all estimated measures.

The intention-to-treat approach to the analysis population will be applied in all cases unless specified otherwise. In case more than 10% of the data is missing, maximum likelihood imputations will be performed based on demographical data and the scores from the pretreatment assessment. The between-group differences at week 11 (primary endpoint) for the primary (YGTSS-TTS) and secondary outcome measures, an analysis of covariance (ANCOVA) with pre-score of the measure as covariate will be calculated. For ATQ and WSAS that are collected weekly, mixed effect models will be applied with random intercept and random slope. Chi squared tests will be calculated to explore the between-group differences in proportions of responders and long-term responders at all endpoints.

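### Above 10% missing, the stated imputation leaves out treatment arm and on-treatment data, so the week-11 effect shrinks by about the missing fraction

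*Protocol article*

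**What the plan says.** Section 2.7 (Statistical methods) of the protocol article sets the analysis population first: "The intention-to-treat approach to the analysis population will be applied in all cases unless specified otherwise". It then gives a conditional rule for missing data. The condition is "In case more than 10% of the data is missing", and the action is that "maximum likelihood imputations will be performed based on demographical data and the scores from the pretreatment assessment". For the week-11 comparison of the primary outcome (YGTSS-TTS) and the secondary outcomes, "an analysis of covariance (ANCOVA) with pre-score of the measure as covariate will be calculated". ATQ and WSAS have their own mixed models.

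Section 2.4 (Outcomes) shows what is measured between baseline and week 11. It lists the "Adult Tic Questionnaire (ATQ) (also administered weekly" among the self-rated tic measures, and Table 3 adds weekly WSAS and MADRS-S at weeks 3 and 7. The article does not name any of these, or the allocated arm, as an imputation predictor. It also does not say whether imputation is single or multiple.

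Section 2.5 (Sample size) plans for d = 0.5 with 50 per group, 80% power, one-tailed, and 110 in total to allow for 10% drop-out. That allowance equals the level above which imputation starts.

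**The concern.** An imputation model should contain every term of the analysis model that follows it. The term of interest here is treatment arm, and the stated predictor list lacks it. Participants in either arm with the same baseline profile would then get the same predicted week-11 score. Each imputed participant carries a treatment effect of zero, and the ANCOVA averages those zeros with the observed effect.

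The list also passes over the weekly ATQ, which records how a participant's tics were developing before the week-11 rating was lost. Leaving it out does not by itself pull the effect to zero. It does make the missing-at-random assumption harder to defend, and it gives up precision.

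The stake is the primary estimate of a superiority trial sized for d = 0.5. A small excess of drop-out over the planned 10% would bring the rule into force and lower the expected estimate in one step.

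**Working it through.** **The plan's own figure.** With 50 per group, d = 0.5 and a one-sided 5% test, power is 0.804 (normal approximation) or 0.799 (noncentral t), so the stated 80% is reproduced. Allowing for 10% drop-out, 100 / 0.9 = 111.1, or 112 for equal arms, against 110 stated. That is close enough not to matter here.

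**Inputs.** From the article: d = 0.5, 55 per arm, ANCOVA on the baseline score, predictors limited to baseline data. Assumed, because the article gives no figure: baseline-to-week-11 correlation 0.6 (0.0 and 0.8 also tried), 10% to 30% missing at week 11, missing at random.

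**Closed form.** Let m1 and m0 be the missing fractions in the intervention and control arms, and w1 and w0 each arm's share of the observed participants. Without arm in the model, an imputed score has expectation w1·μ1 + w0·μ0 in both arms. Hence

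expected effect = d × (1 − m1·w0 − m0·w1).

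With equal missingness w1 = w0 = 0.5, and this becomes d × (1 − m). With 25% missing in one arm and 10% in the other, the shares are 0.75/1.65 = 0.4545 and 0.90/1.65 = 0.5455. The factor is 1 − 0.25 × 0.5455 − 0.10 × 0.4545 = 0.818, and the effect is 0.409.

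**Simulation** (2000 trials per setting, correlation 0.6, true effect 0.50; MI = 20 multiple imputations with Rubin's rules):

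| Missing | Closed form | MI without arm | MI with arm | Complete-case ANCOVA |
|---|---|---|---|---|
| 10% | 0.450 | 0.445 | 0.496 | 0.497 |
| 15% | 0.425 | 0.420 | 0.495 | 0.495 |
| 20% | 0.400 | 0.394 | 0.495 | 0.495 |
| 30% | 0.350 | 0.351 | 0.507 | 0.507 |
| 25% / 10% | 0.409 | 0.409 | 0.503 | 0.503 |

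Single imputation without arm gives the same means to within 0.002. At 20% missing the effect is 0.399 for correlation 0.0 and 0.398 for 0.8, so the shrinkage hardly depends on that assumption.

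**Coverage of the 95% interval** (the range for single imputation covers a regression-mean fill and one random draw):

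| Missing | Single, no arm | MI, no arm | Single, with arm | MI, with arm |
|---|---|---|---|---|
| 10% | 0.930–0.934 | 0.960 | 0.917–0.920 | 0.948 |
| 15% | 0.911–0.916 | 0.954 | 0.899–0.909 | 0.950 |
| 20% | 0.873–0.888 | 0.950 | 0.878–0.892 | 0.953 |
| 30% | 0.798–0.847 | 0.952 | 0.849–0.867 | 0.954 |

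The two single-imputation columns fall short for different reasons. Without arm, the regression-mean fill at 20% missing has a mean standard error of 0.138, equal to the true spread of 0.138; the estimate is simply in the wrong place. With arm, the estimate is right but the standard error is too small (0.136 against 0.172). Multiple imputation without arm covers because its standard error is too large (0.173 against 0.139), which offsets the bias.

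**Power, one-sided.** MI without arm against MI with arm: 0.874 and 0.916 at 10% missing, 0.825 and 0.897 at 15%, 0.775 and 0.880 at 20%. With a single regression-mean fill without arm at 20%, power is 0.882 against 0.885 for complete cases, so in that variant the harm is to the estimate and its interval, not to the test.

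**Type I error, one-sided, 20% missing, no true effect.** Without arm: 5.3% to 5.6% for single imputation and 2.2% for MI. With arm: 8.5% to 9.5% for single imputation and 5.2% for MI.

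**Drop-out that depends on progress.** In one illustrative scenario (2000 trials), intervention-arm drop-out depended on mid-treatment ATQ, with about 13% missing overall. Complete-case analysis gave 0.54, the stated rule 0.47, and MI with arm and ATQ 0.50 with 95% coverage. The strength of that dependence is assumed.

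**The case against.** The strongest reply is that a condensed article need not list every predictor. The sentence says what imputation is based on, not that nothing else enters, and an unseen analysis plan could add the arm. That possibility stands. But the article does give a predictor list, everything on it precedes randomisation, and no other section adds to it. An analyst who follows the sentence leaves the arm out.

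It also stands that the rule may never be triggered, since planned drop-out is 10% and section 2.4 describes reminders and active contact. ATQ and WSAS, analysed by mixed models, need not depend on it.

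A reader might infer four stronger things that the article does not support:

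- *That the intervals under-cover.* This requires single imputation. It is a common meaning of maximum likelihood imputation, but the text does not fix it, and multiple imputation without arm covers at about 0.95 to 0.96 in the coverage table.
- *That the rule is always worse than not imputing.* It is when complete-case ANCOVA is unbiased. In the ATQ-dependent scenario the rule is off by 0.03 and complete cases by 0.04.
- *That responder status cannot be imputed, because CGI-I is* "the latter not administered at pre-treatment". The rule refers to baseline scores in general, and Table 3 has YGTSS and CGI-S at enrolment.
- *That the trial risks a false claim of superiority.* Leaving out arm pulls towards no effect.

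**Conclusion.** The concern holds in a limited form. As stated, the rule omits the treatment arm and the on-treatment ratings, and it would shrink the week-11 effect by about the missing fraction: from 0.50 to about 0.45 just above the trigger, 0.42 at 15% and 0.40 at 20%. This rests on data missing at random, equal missingness by arm, and the sentence being followed literally; the baseline correlation hardly matters.

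The direction is conservative. The cost is an understated effect and, depending on how imputation is done, lost power or intervals that are too often wrong. Type I error is not materially raised. Because the rule bites only above 10% missing and the bias is moderate, this is a correction to make before analysis rather than a threat to the trial's validity.

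**What to change.** Replace the imputation sentence in section 2.7 with wording such as: *Missing week-11 outcomes are handled by multiple imputation with Rubin's rules, or by a likelihood-based repeated-measures model, whatever the percentage missing. The model includes treatment arm, the baseline score of the outcome, and a short summary of on-treatment ATQ (for example the mid-treatment and last observed values).* With multiple imputation, the week-11 ANCOVA itself stays as it is.

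Three cautions:

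- Adding arm to a single imputation is not enough. It removes the bias, but coverage stays at 0.88 to 0.89 and one-sided type I error rises to 8.5% to 9.5% at 20% missing.
- Keep the ATQ summary small. Entering every weekly score with about 55 per arm risks an over-fitted model.
- Do not use 14-month data to impute week-11 outcomes. Controls may have received I-BT by then (section 2.3.2), and analysis is due to start in July 2025 while the last follow-up is expected in July 2026 (section 5).

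The cost is a wording change, recorded where the article says protocol modifications will be described (section 2.1), and modest extra programming. No new data are needed.

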### Sample size

2.5

The within-group effect size in the feasibility trial was Cohen's d = 0.49 (21). As tic severity is known to fluctuate over time, we expect a certain amount of improvement in the control condition. However, we do not expect it to be as large as in the two previous ERP-based I-BT studies in children (19, 20), because the control group in those studies was much more potent. Furthermore, the participants in our previous adult pilot trial improved as much as the participants in a previous adult trial (18), but their pre-treatment tic severity was unexpectedly low, making the overall pre-to-post-treatment effects small. In the current trial, we expect the participants to have a more representative pre-treatment tic severity and their improvement to the primary endpoint is expected to be larger. In sum, we assume the between-group effect-size measured with Cohen's d to be around 0.5. With *n* = 50 participants in each group we will achieve 80% power to detect the effect of between-group Cohen's d = 0.5 (one-tailed test). A total sample size of *n* = 110 will allow for 10% drop-out rate.

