### Randomization and blinding

2.6

The participants will be starting treatment in cohorts. Every time a cohort is ready to start, the online service random.org will be used to create a randomized list of the participants included into the cohort. The list will be emailed to a person not associated with the research group with the instruction to choose the following: (1) where an imaginary line dividing the cohort into two approximately equal groups should be drawn, and (2) whether the group above the line should be marked with “I” (meaning intervention) or “K” (meaning control). The outcome assessors will be blinded to the allocation of the participants, and they will be asked to guess the allocation after each assessment. The frequency of correct guesses will be reported as a measure of blinding integrity.

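### Allocation is balanced within each starting cohort, but no planned analysis contains cohort; if cohorts differ, the intervals come out somewhat too wide and the tests conservative

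*Protocol article*

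**What the plan says.** **Randomisation (protocol article, section 2.6).** Participants start in cohorts, and each cohort is randomised on its own: "Every time a cohort is ready to start, the online service random.org will be used to create a randomized list of the participants included into" that cohort. A person outside the research group then chooses "where an imaginary line dividing the cohort into two approximately equal groups should be drawn", and which side of it is the intervention group. This is restricted randomisation with starting cohort as the stratum.

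**Analysis (section 2.7).**
- Week-11 primary and secondary outcomes: "an analysis of covariance (ANCOVA) with pre-score of the measure as covariate will be calculated".
- Weekly scales: "For ATQ and WSAS that are collected weekly, mixed effect models will be applied with random intercept and random slope".
- Responders: "Chi squared tests will be calculated to explore the between-group differences in proportions of responders and long-term responders at all endpoints".

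None of these names cohort.

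**Error rate and power.** Section 2.7 states: "The significance level for all statistical tests will be *α* = 0.05", without saying whether tests are one- or two-sided. Section 2.5 states that with 50 per group "we will achieve 80% power to detect the effect of between-group Cohen's d = 0.5 (one-tailed test").

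**The concern.** When allocation is balanced within strata, differences between strata largely cancel out of the treatment comparison. An analysis that omits the strata leaves those differences in the residual variance, so it reports more uncertainty than the design produces.

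Cohort differences are plausible here. Inclusion runs from February 2024 to about January 2025 (section 5). Section 2.4 describes raters ranging from psychiatrists to supervised students, and section 2.5 says tic severity fluctuates over time. How large such differences are is not known.

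At stake are the width of the 95% confidence intervals promised in section 2.7 and a few points of power. The sample size reaches 80% only with a one-tailed test.

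**Working it through.** **1. The plan's own figure.** Inputs from section 2.5: 50 per arm, d = 0.5, one-tailed, with α = 0.05 from section 2.7.

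- Non-centrality: 0.5 × √(50/2) = 2.5.
- One-sided power: Φ(2.5 − 1.645) = Φ(0.855) = 0.804 (noncentral t: 0.799). The stated 80% reproduces.
- Two-sided power at the same size: Φ(2.5 − 1.96) = Φ(0.54) = 0.705 (noncentral t: 0.697).

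Leaving out cohort does not undermine the stated 80%.

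**2. What omitting cohort does.** Take N = 100 evaluable, K = 10 equal cohorts (assumed), exact halves within cohort, total outcome variance 1, a share ICC between cohorts (assumed), and no credit for the pre-score.

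- True SD of the estimate = √[4(1 − ICC)/N], with or without cohort in the model.
- SE reported without cohort ≈ √(4·MS/N), where MS = (1 − ICC) + ICC × (N − N/K)/(N − 2).

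At ICC 0.10:

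- True SD = √(4 × 0.90/100) = 0.190.
- MS = 0.90 + 0.10 × 90/98 = 0.992, so the reported SE = √(4 × 0.992/100) = 0.199.
- Ratio = 0.199/0.190 = 1.05, so the reported SE is about 5% too large.
- Two-sided type I error = 2[1 − Φ(1.96 × 1.05)] = 0.040.
- Two-sided power without cohort = Φ[(0.5 − 1.96 × 0.1992)/0.1897] = Φ(0.578) = 0.718.
- Two-sided power with cohort = Φ(0.5/0.1897 − 1.96) = Φ(0.676) = 0.750.
- Difference: about 3 points.

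**3. Simulation of the same setting** (10 cohorts, N = 100, 5,000 runs per cell; pre-score only → pre-score plus cohort).

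| ICC | Power, one-sided | Power, two-sided | Type I error, two-sided |
|---|---|---|---|
| 0 | 0.800 → 0.800 | 0.686 → 0.687 | 0.048 → 0.049 |
| 0.05 | 0.802 → 0.813 | 0.701 → 0.712 | 0.040 → 0.044 |
| 0.10 | 0.806 → 0.826 | 0.698 → 0.731 | 0.039 → 0.049 |
| 0.20 | 0.812 → 0.859 | 0.711 → 0.772 | 0.035 → 0.054 |

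The Monte Carlo standard error is about 0.003 for type I error, √(0.05 × 0.95/5000), and about 0.006 for power near 0.8, √(0.8 × 0.2/5000). The simulated SD of the estimate at ICC 0.10 is 0.191 under both models. With 6 cohorts, two-sided power moves from 0.705 to 0.721 at ICC 0.05 and from 0.709 to 0.738 at ICC 0.10.

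**4. With a useful pre-score** (correlation 0.6, assumed; 10 cohorts of 10). At ICC 0.10 the pre-score-only SE is 0.159 against a true SD of about 0.15. Type I error is 3.7% against 5.0%, and power 0.895 against 0.920. At ICC 0 the models are level (0.873 v 0.870).

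**5. Slightly unequal splits** (off by up to one person, no pre-score correlation). One-sided power goes from 0.807 to 0.824 at ICC 0.10, and from 0.789 to 0.781 at ICC 0. The second is the price of a needless cohort term: about 1 point.

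**6. Responders** (assumed 20% v 45%, 10 cohorts, two-sided; plain chi-squared → CMH by cohort).

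- No cohort effect: power 0.775 → 0.775.
- Cohort SD 0.5 on the logit scale: 0.754 → 0.763.
- Cohort SD 0.8: 0.694 → 0.734.

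Under the null, CMH rejected in 4.9% to 5.7% of runs.

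A logistic model with fixed cohort effects behaves worse. The true odds ratio is (0.45/0.55)/(0.20/0.80) = 3.27, but the adjusted estimate is about 3.7 to 3.9 with 10 or 11 cohorts of 10, and 4.76 with 20 cohorts of 5. Its type I error is 5.7% to 7.9%.

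**The case against.** The best defence is that the stated analysis is valid. Its error is in the safe direction, and no false claim of efficacy can follow from it. The size depends on a cohort number and an ICC that the documents do not give. Several features argue for a small ICC: one site and one online programme (section 2.1), common eligibility thresholds and national recruitment (section 2.2), therapists who treat both arms under supervision (section 2.3.3), and rater training with co-ratings every six months (section 2.4). With the pre-score counted, power may already be well above 80%. Section 2.7 also does not say that the pre-score is the only covariate, and a fuller analysis plan could add cohort.

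Most of this stands, and it limits the point to a modest refinement. It does not remove it: section 2.7 names the covariate and the responder test, so the choice is stated in the article, and including cohort costs almost nothing even if the ICC is near zero.

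Three stronger readings are tempting and not supported:

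- **That the trial discards precision it paid for.** The estimate's true SD is the same with and without cohort under equal splits. Only the reported SE and the test change.
- **That the results would be biased or the test too liberal.** Type I error falls below 5%, and near-equal splits give no expected bias.
- **That CGI-I is left without a workable analysis because it is "the latter not administered at pre-treatment".** An ANCOVA on its own pre-score is indeed impossible, but section 2.4 uses CGI-I to define responders, and section 2.7 gives responders their own test. This is loose wording and separate from cohort.

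**Conclusion.** The point holds as a matter of efficiency and honest interval width, not validity. Cohort is a randomisation stratum under section 2.6 and is absent from every analysis named in section 2.7. If cohorts differ, standard errors are overstated by about 5% at ICC 0.10, and the power lost is about 2 to 3 points there, about 1 to 2 at ICC 0.05 and none at ICC 0. At ICC 0.20, a value the documents give no reason to expect, it would be about 5 to 6 points. These figures assume about 10 cohorts, about 100 evaluable participants and d = 0.5. A strongly predictive pre-score raises overall power and can make the gain smaller.

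**What to change.** Before the week-11 data are analysed:

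- Add starting cohort to the week-11 ANCOVA and to the ATQ and WSAS mixed models, as a random intercept or as a fixed effect. If fixed, state a rule for merging very small cohorts.
- Replace the plain chi-squared responder tests with a CMH test stratified by cohort, and report the common odds ratio with its 95% confidence interval. This also serves the odds-ratio reporting already promised in section 2.7.
- Do not use a logistic model with many fixed cohort effects, for the reasons shown in step 6.

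The change needs no new data, since cohort membership is already known, and section 2.1 provides a route for posting modifications publicly. The cost is a sentence or two in the analysis plan and its code and a few degrees of freedom. If cohorts do not differ and splits are slightly unequal, up to about 1 point of power is lost.

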**Methods:**

This single-blind randomized controlled superiority trial including 110 participants will compare internet-delivered BT (I-BT) primarily consisting of exposure and response prevention (ERP) to a control condition consisting of internet-delivered general psychological support. The primary aim of the trial is to evaluate whether ERP-based I-BT is superior to the control condition in reducing TS/CTD symptoms. The primary outcome measure is the Yale Global Tic Severity Scale - Total Tic Severity score administered by blinded raters at primary endpoint 11 weeks after the treatment start. Secondary endpoints occur at week 23 and 14 months after the treatment start, and the secondary outcomes include tic-related impairment, rates of responders, self-rated tic severity, symptoms of depression, quality of life and cost-effectiveness. Data on dropout rates and adverse events is also collected.

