The primary aim of the study is to investigate whether guided internet-delivered ERP-based BT is superior to an active control condition consisting of guided internet-delivered general psychological support in reducing TS/CTD symptoms. We hypothesize that, compared to the control group, participants in the treatment group will show greater reduction in tic severity, as measured with Yale Global Tic Severity Scale - Total Tic Severity subscale (YGTSS-TTS) (22) at the primary endpoint (post treatment or week 11 after treatment start).

The secondary aim at the primary endpoint (week 11 after the start of the treatment) is to compare the two arms regarding:
(1)Tic-related impairment(2)Rates of responders(3)Self-rated tic severity(4)Symptoms of depression(5)Quality of life(6)Cost-effectivenessThe third aim is to evaluate long-term maintenance of gains. We hypothesize that the intervention condition will be superior to the control condition at week 23 after the treatment start (better response, less severe symptoms, higher quality of life) regarding all outcome measures and that the results will be maintained in the intervention group at the 14-month follow-up. The fourth aim is to evaluate the cost-effectiveness of the intervention from the healthcare organization payer perspective, the healthcare system perspective, and the societal perspective.

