#### Control condition: internet-delivered general psychological support

2.3.2

Participants who are randomized to the control group will receive access to brief psychoeducational content about TS/CTD in the platform in combination with general psychological support from a therapist. The materials will be divided in two chapters. Chapter 1 will cover the topics of what tics are, and the different ways stress can influence the symptoms. Chapter 2 will focus on supporting stress management and healthy lifestyle habits related to food, sleep, and physical activity. No active BT components (i.e., ERP, HRT, applied relaxation) are provided to the participants in the control group. The therapists will welcome the participants to the treatment, encourage them to engage in the treatment content and to reach out to the therapist if they have any questions. Thereafter, the therapists will only reply to the participants’ messages without taking any contact initiative themselves (unless there is an indication of severe deterioration or severe depressive symptoms or suicidal ideation requiring medical attention). The aim of the control condition is to control for basic therapist attention, relevant disorder-specific content, and the passage of time. The participants in the control group who wish to have additional help will have an opportunity to receive I-BT after the data from the first long-term follow-up (week 23 after the start of the treatment) are collected.

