### Outcomes

2.4

If not specified otherwise, the outcome measures will be collected at pre-treatment, at week 11 counting from the start of the treatment (post-treatment, primary endpoint), week 23 (3 months after the end of the treatment), and 14 months after the treatment start (12 months after the end of the treatment) (Table 3).

**Table 3 T3:** Overview of the recruitment, treatment, and assessment points and measures.

	Enrolment	Allocation	Pre-treatment	Week 1–3	Week 4–7	Week 8–10	Week 11 (post-treatment, primary endpoint)	Week 23	14-month follow-up
Enrolment									
Eligibility screen	X								
Informed consent	X								
Allocation		X							
Treatment									
ERP				X	X	X			
Control condition				X	X	X			
Clinician-administered measures									
DSM-5 criteria for TS/CTD	X								
SCID-5	X								
MINI	X								
YGTSS	X						X	X	X
CGI-S	X						X	X	X
CGI-I							X	X	X
iiPAS					X		X		
Self-rated measures									
ATQ1	X		X	X	X	X	X	X	X
RAADS-14			X						
ASRS			X						
PUTS			X						
MADRS-S^b^	X		X	X	X		X	X	X
AUDIT	X								
DUDIT	X								
WSAS^a^			X	X	X	X	X	X	X
GTS-QoL			X				X	X	X
AQoL-6D			X				X	X	X
TIC-P			X				X	X	X
Negative effects							X	X	
Other adverse events				X	X		X	X	
CEQ					X				
WAI-SR					X				
Time spent on the programme^a^				X	X	X	X	X	X

AQoL-6D, assessment of quality of life—6 dimensions; ASRS, adult ADHD self-report scale; ATQ, adult tic questionnaire; AUDIT, alcohol use disorders identification test; CEQ, credibility and expectancy questionnaire; CGI-I, clinical general impression—improvement; CGI-S, clinical general impression—severity; DUDIT, drug use disorders identification test; ERP, exposure with response prevention; GTS-QoL, gilles de la Tourette syndrome—quality of life scale; iiPAS, internet interventions patient adherence scale; MADRS-S, montgomery—asberg depression rating scale—self-rated; MINI, the mini international neuropsychiatric interview; PUTS, premonitory urge for tics scale; RAADS-14, ritvo autism and asperger diagnostic scale; SCID-5, OCD and related disorders section of the Structured Clinical Interview for DSM-5; TIC-P, treatment inventory of costs in patients with psychiatric disorders; TS/CTD, Tourette syndrome/chronic tic disorder; WAI-SR, working alliance inventory—self-rated; WSAS, work and social adjustment scale.

^a^
Administered weekly during the 10-week treatment.

^b^
Administered at week 3 and 7.

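### The planned 14-month between-arm responder test comes after controls may take up I-BT, so it no longer estimates I-BT versus support and answers none of the stated hypotheses

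*Protocol article*

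**What the plan says.** Four statements in the protocol article bear on this point.

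- Statistical methods (2.7): "Chi squared tests will be calculated to explore the between-group differences in proportions of responders and long-term responders at all endpoints". Intention to treat is the default for all analyses, and this section states no exception or handling for control participants who later receive I-BT.
- Abstract, Methods: "Secondary endpoints occur at week 23 and 14 months after the treatment start". Table 3 schedules the CGI-I at week 11, week 23 and 14 months. According to Outcomes (2.4), participants with one of the two best improvement ratings "on the CGI-I will be classified as treatment responders". The 14-month visit therefore falls within the scope of the planned tests.
- Control condition (2.3.2): control participants "will have an opportunity to receive I-BT after the data from the first long-term follow-up (week 23 after the start of the treatment) are collected". The offer is for those who want it: "The participants in the control group who wish to have additional help". The abstract's Discussion and section 4 repeat the offer. No expected uptake is given.
- Introduction (aims): superiority over control is hypothesised at week 23. For the last visit, the hypothesis is that "results will be maintained in the intervention group at the 14-month follow-up".

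**The concern.** Up to week 23 the arms differ as randomised: I-BT against general support. After week 23 an unknown share of the control arm may receive the intervention under test. A between-arm responder test at 14 months then no longer measures the effect of I-BT against support.

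The aims do not ask for that test either. At 14 months they pose a question about one arm only: whether its gains last. The analysis sentence and the hypothesis therefore do not match.

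What is at stake is interpretation. A small or non-significant 14-month difference could be taken as fading benefit when the intervention arm had kept its gains and the controls had caught up through delayed I-BT. That would obscure the durability question that the third aim sets out to answer.

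**Working it through.** **The plan's own figure.** Sample size (2.5) states 80% power for d = 0.5 with 50 per group, one-tailed. Check: 0.5/√(2/50) = 2.50; 2.50 − 1.645 = 0.855; Φ(0.855) = 80.4%. The figure reproduces. It concerns the mean difference in tic severity, so it is no benchmark for responder tests and supplies only the n of 50 per arm used below.

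**Timing.** Fourteen months is about 14 × 52/12 ≈ 61 weeks, so about 38 weeks separate week 23 from the last visit. The trial's I-BT course lasts 10 weeks. If delayed I-BT takes about as long (an assumption), a control participant can complete it well before 14 months.

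**Effect on the responder comparison.** From the article: 50 per arm, α = 0.05. Assumed, because the article gives none of these: responder rates without cross-over of pI = 40% and pC = 15%; uptake u varied from 0 to 100%; uptake unrelated to earlier response; controls who take up I-BT reach the intervention-arm rate.

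- Control rate at 14 months: pC′ = pC + u(pI − pC)
- Power = Φ[(d − 1.96·SE0)/SE1], with d = pI − pC′, p̄ = (pI + pC′)/2, SE0 = √(2p̄(1 − p̄)/50) and SE1 = √((pI(1 − pI) + pC′(1 − pC′))/50), two-sided

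At u = 50%: pC′ = 0.15 + 0.5 × 0.25 = 0.275, d = 0.125, p̄ = 0.3375, SE0 = 0.0946, SE1 = 0.0937. Then (0.125 − 1.96 × 0.0946)/0.0937 = −0.64 and Φ(−0.64) = 26%.

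| Uptake | Control rate | Difference (points) | Power, 40% vs 15% | Power, 50% vs 20% |
|---|---|---|---|---|
| 0% | 15% | 25 | 81% | 89% |
| 25% | 21.25% | 18.75 | 53% | 64% |
| 50% | 27.5% | 12.5 | 26% | 33% |
| 75% | 33.75% | 6.25 | 9% | 11% |
| 100% | 40% | 0 | no difference to detect | no difference to detect |

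The control-rate and difference columns refer to 40% vs 15%. The last column repeats the calculation for a second assumed pair of rates.

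**If non-responders are the ones who accept.** The offer is aimed at people who want more help, so uptake may be concentrated among controls who have not responded. Suppose only they take it up, respond at 40%, and earlier control responders stay responders. Then pC′ = 0.15 + 0.85 × u × 0.40, with u now the uptake among control non-responders:

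- u = 50%: 32%, an 8-point difference, power 13%
- u = 75%: 40.5%, the difference is gone
- u = 100%: 49%, the direction reverses (40% vs 49%)

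**Long-term responders.** Section 2.4 grants this status only to participants who keep responder status at later follow-ups. A control who first responds after taking up I-BT has no earlier status to keep. Cross-over can therefore alter this count only among controls who had already responded by week 23, for example by helping them stay responders.

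**The case against.** The strongest reply has five parts.

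- **The arms remain randomised.** A reader might infer that the 14-month test compares treated with treated, or that no randomised contrast is left. The article does not support either reading. I-BT is optional for controls and uptake is not stated, so treated versus treated would hold only at full uptake. Under intention to treat there is still a valid randomised comparison, of immediate I-BT against support with later optional I-BT. This stands. What changes is the question that the comparison answers.
- **Long-term responders are largely protected.** A reader might infer that this count is as contaminated as the plain responder count. By its definition it is not, as shown above. This stands.
- **The test is exploratory.** It concerns a secondary outcome at the last visit, no stated hypothesis depends on it, and the cross-over offer is openly disclosed. This stands and limits the severity. It does not remove the mismatch between the analysis sentence and the aims.
- **The power figures are illustrative.** The rates and uptake are assumed, and the trial was not powered on responders. This is correct. The likely direction of the bias, toward no difference, does not depend on the particular rates; the size does.
- **Detail may sit in an analysis plan or in the flow chart, neither of which is shown.** This would answer a complaint about silence. Here the article itself fixes the time points, and that choice conflicts with its own hypothesis and cross-over offer.

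Two further complaints are tempting and should not be pressed. Long-term status cannot exist at week 11, but the sentence reads naturally as applying each status where it is defined. The article also states no 14-month between-arm model for ATQ or WSAS, so the point does not extend to them.

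**Conclusion.** The point holds for the plain responder comparison at 14 months. As written, the plan includes a between-arm test that no longer estimates I-BT versus support, that no stated hypothesis calls for, and that is likely biased toward no difference.

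Its size depends on quantities the article does not give. With 50 per arm and random uptake, power falls from 81–89% with no cross-over to 53–64% at 25% uptake, 26–33% at 50% and 9–11% at 75%, across the two assumed pairs of responder rates. If mainly non-responding controls accept, the dilution is faster and the difference can vanish or reverse before or at full uptake.

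The severity is moderate. The week-11 primary analysis and the week-23 comparisons precede the offer and are unaffected, and the long-term responder comparison is only partly exposed.

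**What to change.** Amend the responder sentence in section 2.7 as follows.

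- Limit between-arm responder tests of I-BT versus support to weeks 11 and 23.
- At 14 months, report maintenance in the intervention arm (responder and long-term responder proportions with 95% confidence intervals), which matches the stated hypothesis.
- Report how many control participants took up I-BT before the 14-month assessment.
- If a 14-month between-arm contrast is kept, present it descriptively and label it immediate versus delayed/optional I-BT. Avoid comparing controls by whether they took up I-BT as if those groups were randomised, because they are self-selected.

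The cost is a sentence or two of text. The 14-month assessments and the design are unchanged; uptake needs only a count of who started I-BT. Section 5 puts the start of analysis in July 2025 and the last follow-up in July 2026, so on those dates the change can precede any 14-month analysis. Section 2.1 already names OSF and ClinicalTrials.gov as the places to record modifications.
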